### Study sample and recruitment

The study population comprised children close to 12 months and one of their parents. To be included in the study, parents had to have a child born between August 2016 and April 2017 and the parents had to be literate in Norwegian. Participants were recruited via Facebook. A short video was launched on Facebook with a link to the project website containing information about the project and the opportunity to sign up. The recruitment period lasted 5.5 months from mid-August 2017 to January 2018. In total 404 parents were recruited. The month before the child reached age 12 months, the enrolled parent received an e-mail with a link to a questionnaire. Three reminders on e-mail were sent to non-responders the following weeks. We included a total of 298 parents who responded to more than half of the survey questions. After they had completed the baseline questionnaire, participants were randomized according to an SPSS-generated randomization list prepared of [name], of 500 to the intervention and control group (SPSS version 24.0). The first author was the one who enrolled participants and assigned participants to the intervention group and control group. Among the participants who answered baseline and post intervention questionnaires, ten participants were selected to receive a gift card of 1000 Norwegian kroners. Demographic characteristics of the sample are provided in Table 1.

**Table 1 Tab1:** Characteristics of participating parents and children

		Intervention (*n* = 148)	Control (*n* = 150)
Parents (*N* = 298)	Mother/father/other (n)	144/4/0	148/0/2
	Age (year), mean (SD))	31.5 (4.4)^a^	31.9 (4.0)
	Height, mean kg (SD)	168.7 (6.0)	168.1 (5.9)^b^
	Weight, mean cm (SD)	70.8 (14.3)	71.1 (14.8)^b^
	BMI, mean (SD)	24.9 (4.6)	25.1 (4.8)^b^
	Two adult household (%)	98.0	96.7
	Family members (n), mean (SD)	3.60 (1.0)	3.65 (0.87)
	Born in Norway (%)	89.2	83.2^a^
Education		^a^	^a^
	Upper-level secondary school or less (%)	12.2	11.4
	College/university (≤4 years) (%)	31.3	36.9
	College/university (> 4 years) (%)	56.5	51.7
Geographic residence			
	Northern Norway (%)	4.5	6.7
	Central Norway (%)	10.8	10.7
	Western Norway (%)	23.0	20.7
	Southern Norway (%)	16.2	20.0
	Eastern Norway (including Oslo) (%)	44.6	42.0
Child			
	Age (months (SD))	10.9 (1.3)	10.8 (1.2)
	Girls (%)	46.6	43.3

^a^one missing, ^b^two missing

Sample size was calculated for one of the primary outcomes, child diet quality. As we have no data on healthy eating score for the Norwegian toddler population, we used the data of Angelopoulos and colleagues [43], which showed a mean healthy eating score of 60.5 among children (SD 9.0). We considered a 3-point difference in such a score between the intervention and control groups to be relevant from a public health perspective. We calculated that 142 children in each group would be required to demonstrate statistical significance with a statistical power of 80% and α of 5%. Assuming loss to follow-up of 40%, we aimed to recruit 237 parents in each group.

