### Primary outcomes

Primary outcomes of the study are child diet quality and food variety assessed at baseline and after the intervention.

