Child’s diet	PSO, IC	Overall diet Food Variety (Continuous)	Food intake (core-and non-core foods) Healthy eating index	FFQ based on nationwide Norwegian diet survey among 12-month-old children [12] and the MoBa-study [55]	At baseline, 18, 24, and 48 months
SECONDARY OUTCOME Eating environment					
Child level: food preferences	SSO, IC	Food neophobia (Continuous)	Rating the child’s willingness to try new foods	The food neophobia scale [61]	At baseline, 18, 24, and 48 months
Parental level: feeding practices	SSO, IC	Feeding style and feeding practices (Categorical)	Under−/over-eating, hunger, infant cues. Feeding attitudes, practices, perceptions or concerns about weight	Comprehensive feeding practices [62, 63]	
	SSO, IC	Food neophobia (Continuous)	Rating the parent’s willingness to try new foods	The food neophobia scale [61]	
	SSO, IC	Self-efficacy (Categorical)	Parental self-efficacy in eating situations	Feeding self-efficacy [64]	
Family level: meal setting	SSO, IC	Frequency of shared meals (Categorical)	Frequency of meals and meal distractions	Questionnaires from the nationwide Norwegian diet survey among 12-month-old children [12] and items developed for this study	
Food environment					
Macro-level: grocery shopping	SSO, IC	Food choice and awareness of food environment (Categorical)	Planning, grocery shopping, what influences food choice	FCQ [65] SCQ: some elements made for this study, are based on theory of Wansink [51], and additional items developed for this study	At baseline, 18, 24, and 48 months
Micro-level: Home	SSO, IC	Availability and accessibility of food (Categorical)	Availability and accessibility of non-core and core foods Food preparation and planning	Questions developed for this study and items from Helland and colleagues [66]	
	SSO, IC	Meal management and food coping strategies (Categorical)	Self-efficacy related to meal management and food coping strategies	Meal management and food coping strategies questionnaire [67]	
OTHER					
Child anthropometrics	SSO	Anthropometric outcome (Continuous)	Height and weight	Self-reported, but measured at scheduled health center visits	At baseline, 18, 24, and 48 months
Parental characteristics	SC	Height and weight Demographics Socioeconomic status Food behaviors	Height and weight Education, occupation and food intake	Self-reported on questionnaire and simple FFQ [12]	

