### Statistical analysis plan

For this protocol paper we present descriptive statistics of sample characteristics. All analyses were performed by using IBM SPSS Statistics 25.0.

Intervention effects on child diet, will be examined by use of mixed models (Linear Mixed Models and Generalized linear mixed models) with time as within factor (differences between baseline and post-test, follow-up 1, 2 and 3, respectively) and condition (intervention group, control group) as between-group factor. All models of pre-post outcomes will be adjusted for baseline values to account for regression to the mean effects. Using mixed models allows for use of incomplete data at the different follow-ups and thereby increase statistical power. We will present both crude and adjusted results. Intervention effects on both primary and secondary outcomes will be adjusted for the following variables: parental SES, BMI and age, and child gender and age (variables known from previous research to potentially confound such associations). To examine potential moderating effects such as parental SES (lower versus higher education level), a three-way interaction effect (time*condition*moderator) will be investigated for each outcome. As loss to follow up is expected, loss to follow-up-analyses will be performed, analyzing those lost to follow up compared to those remaining in the study. This will be done to identify if there are characteristics specific of those lost to follow up important to interpret the results.

The data will be stored securely on a password-protected computer with no connection between the data and personally identifiable information. The data will be available after project completion.

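### Two primary outcomes, one sized at the full 5%, and no rule for combining them: if either suffices, the primary claim carries about a 7–10% false-positive rate

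*Protocol article*

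**What the plan says.** The Primary outcomes section states: "Primary outcomes of the study are child diet quality and food variety assessed at baseline and after the intervention". Table 3, under Measures and instruments, lists both in its primary-outcome row as "Overall diet Food Variety (Continuous"), collected at baseline and at 18, 24 and 48 months.

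The sample-size paragraph in Study sample and recruitment says: "Sample size was calculated for one of the primary outcomes, child diet quality". It takes an SD of 9.0 from an earlier study in children and sets the target effect: "We considered a 3-point difference in such a score between the intervention and control groups". It concludes: "We calculated that 142 children in each group would be required to demonstrate statistical significance", "with a statistical power of 80% and α of 5" per cent. That is the only place where alpha appears.

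The section headed Statistical analysis plan describes mixed models with contrasts from baseline to post-test and to the later follow-ups. It says "We will present both crude and adjusted results" and then states that effects on primary and secondary outcomes will be adjusted for a named list of covariates. It does not say how the two primary outcomes combine into one conclusion.

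**The concern.** With two primary outcomes, the 5% used for sizing is the error rate of the trial's conclusion only under certain rules: a fixed order, a split of alpha, or a requirement that both succeed. The article states none of these. As written, a significant result on food variety alone could be presented as a positive trial, although the 5% was spent in full on diet quality.

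The sample size also limits which rule can be adopted later:

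- An equal split of alpha would leave 142 per group short of 80% power.
- Requiring both to succeed would hold the error rate, but joint power cannot exceed the power for diet quality, and no calculation for food variety is shown.
- Testing diet quality first is the one usual rule that fits the calculation as it stands.

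The choice should be on record before outcome data are compared by arm. Made afterwards, it can look data-driven.

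**Working it through.** **Inputs from the article.** Difference 3 points, SD 9.0, alpha 5%, power 80%, loss 40%, 298 randomised (148 and 150). Sidedness is not stated.

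**1. The stated sample size.** n per group = 2 × (z₁₋α/₂ + z₁₋β)² × SD² / difference² = 2 × (1.960 + 0.842)² × 81 / 9 = 141.3, rounded up to **142**. A one-sided 5% test would give 112, so the figure implies a two-sided 5% test spent wholly on diet quality. Inflated for loss: 142 / 0.6 = 236.7, rounded up to **237**. Both figures are reproduced.

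**2. Either outcome suffices, one visit, two-sided 5% each.** If independent: 1 − 0.95² = **9.75%**. For correlated test statistics, the probability that at least one of two standard normals exceeds 1.96 in absolute value was simulated (1,000,000 draws). The correlations are assumptions:

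| Correlation between outcomes | False-positive rate |
|---|---|
| 0 | 9.75% (exact) |
| 0.5 | 9.1% |
| 0.7 | 8.3% |
| 0.8 | 7.8% |
| 0.9 | 7.0% |

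Both outcomes come from the same parent-reported food frequency questionnaire, so the higher correlations cannot be excluded.

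**3. Both must be significant.** The rate cannot exceed 5%, so there is no inflation.

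**4. What the possible rules do to the sample size.**

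- *Equal split, 2.5% each, two-sided:* n = 2 × (2.241 + 0.842)² × 9 = 171.1, rounded up to 172; 172 / 0.6 = 286.7, rounded up to 287. At 142 per group the standardised effect is 3 / (9 × √(2/142)) = 2.809, and power is Φ(2.809 − 2.241) = **71.5%** instead of 80%.
- *Fixed sequence, diet quality first:* diet quality keeps the full 5%, so 142 and 237 are unchanged.

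**5. Power at the size achieved (assumption-laden).** Applying the planned 40% loss to 298 gives 298 × 0.6 / 2 = 89.4, about 89 per arm. The article does not state this number. With no gain from baseline adjustment, the standardised effect is 3 / (9 × √(2/89)) = 2.224. Power is Φ(2.224 − 1.960) = 60% at alpha 5% and Φ(2.224 − 2.241) = 49% at 2.5%. With an assumed baseline–outcome correlation of 0.5, the effect becomes 2.224 / √0.75 = 2.568, and the figures rise to about 73% and 63%.

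**6. If all three post-baseline visits counted as primary (six tests).** Independent: 1 − 0.95⁶ = 26.5%. Simulated: 22.0% with correlation 0.5 between outcomes and 0.5 between visits; 19.2% with 0.5 and 0.7; 17.7% with 0.7 and 0.7. The range is about 18–27%, and it applies only on a reading that the Primary outcomes section does not suggest.

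**The case against.** The strongest reply is that the article nowhere says food variety is tested at 5% without adjustment. Alpha appears once, for diet quality. A condensed article may leave multiplicity rules to a full protocol or analysis plan that is not shown, and a both-must-succeed rule would remove the problem. This stands in part: the inflation is conditional, and silence on a detail would not by itself be a finding. But the article does fix two primary outcomes and a calculation that gives the whole 5% to one of them. Its own analysis section goes into models, covariates, moderators and attrition without saying how the two combine.

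A reader might go further and infer an error rate above 20%, because Table 3 schedules the primary outcomes at three post-baseline visits. The document does not support that as the plan's error rate. The Primary outcomes section most naturally places the primary assessment after the intervention, and Study design separates the post-intervention questionnaire from the two follow-ups. Table 3 is a collection schedule. The analysis section plans later contrasts but does not say that success at any of them is a primary success. Even on that reading, the rate falls below 20% when visits are highly correlated.

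A reader might also count the crude and adjusted results as two chances of success. The article says that effects on the primary outcomes will be adjusted, which points to the adjusted model as the planned estimate, although it is not labelled as such. The crude/adjusted choice is therefore not shown to be a source of inflation.

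Finally, a fixed sequence is one of several valid remedies. That is true; it is preferred here because it matches the existing calculation.

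**Conclusion.** The concern holds in a limited form. Two primary outcomes are named, the trial is sized on one at the full 5%, and no rule joins them. If either outcome at post-intervention suffices, the false-positive rate of the primary claim is about 7–10% and not 5%. That rests on two assumptions: that either outcome counts as success, and that the outcome correlation lies between 0.9 and 0. The sample-size figures are correct and are not in question. The shortfall in recruitment (298 against 2 × 237 = 474) is a separate matter; it bears on this point only because it makes splitting alpha less attractive. The point is an inexpensive improvement in wording, held with moderate confidence because an unseen plan may already settle it.

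**What to change.** Add a short statement to the analysis section:

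- The primary test is diet quality at post-intervention, two-sided 5%, from the covariate-adjusted mixed model already described.
- Food variety at the same visit is tested at 5% only if diet quality is significant (fixed sequence).
- Results at 24 and 48 months are secondary, and crude results are supportive.

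In the same edit, reconcile the number of follow-ups: the analysis section lists three after the post-test, while Study design and Table 3 give two. If an unseen plan already sets a rule for the two outcomes, state it and confirm that it agrees with the sample-size basis.

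The cost is a few sentences, settled before outcomes are compared by arm. The 142 and 237 per group and the power for diet quality do not change. The one small downside is that food variety cannot be claimed confirmatorily if diet quality is not significant; it can still be reported with its estimate and confidence interval.

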## Discussion

With increasing interest in and use of eHealth programs in health promotion, it is a high public health priority to determine what works best and in what context. For health promotion programs to be successful, it is suggested that interventions should be based on theory, include end-users and stakeholders, and have a randomized controlled design to establish effect.

This study protocol of the Food4toddlers intervention describes a randomized controlled trial targeting an important time span when the child’s preferences for food and eating habits are being established. Our project is in line with The Global Action Plan for the Prevention and Control of NCDs, focusing on early childhood intervention, and alerting and empowering parents in their role as gatekeepers of their child’s diet [56]. We expect that the intervention will provide parents with practical tools and make them more conscious of their child’s food and eating environments.

Laws and colleagues [57] compared three recruitment strategies in recruiting pregnant women or mothers with infants for an mHealth intervention; they found Facebook to be the best strategy. This is in line with the findings of a Norwegian eHealth study recruiting parents with children aged 3–5 months [58]. Facebook was the only recruitment tool used in Food4toddlers which might have a potential to recruit more low SES parents than other recruitment ways [57]. It was not very easy to recruit for this study as evidenced by a lower number of participants than initially aimed for. Because most parents with toddlers in Norway have already returned to work after having completed their maternity (or paternity) leave, we assumed that it would be more difficult to recruit for this study than for studies of younger aged children [58]. The time period from the participants signed up for recruitment (child age 7–12 months) until the baseline questionnaire was sent out, was up to five months, since the age of the child had to be 12 months at baseline. This might be one reason why there was a loss of participants from recruitment to baseline assessment.

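### The sample size calculation is sound as a plan, but power and detectable difference were not restated for the 298 parents actually randomised

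*Protocol article*

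**What the plan says.** Under Study sample and recruitment, the article sizes the trial on one of its two primary outcomes, child diet quality. It borrows a mean of 60.5 and an SD of 9.0 from another study of children, and sets the target difference: "We considered a 3-point difference in such a score between the intervention and control groups to be relevant from a public health perspective". At 80% power and 5% alpha it concludes: "We calculated that 142 children in each group would be required". It then allows for attrition: "Assuming loss to follow-up of 40%, we aimed to recruit 237 parents in each group".

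The same section gives the enrolment achieved. Of sign-ups it says "In total 404 parents were recruited". Of those who went on to randomisation it says "We included a total of 298 parents who responded to more than half of the survey questions". Table 1 gives 148 in the intervention group and 150 in the control group. Recruitment ended in January 2018.

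The Discussion comments: "It was not very easy to recruit for this study as evidenced by a lower number of participants than initially aimed for". It offers reasons for the loss between sign-up and baseline, but no revised power or detectable difference. The Statistical analysis plan section still expects loss to follow-up. It specifies mixed models adjusted for baseline values and says that using incomplete data increases power, without giving a figure.

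**The concern.** The article reports both a power calculation and the final randomised number, and the two no longer fit. The target was 474 (2 × 237) and 298 were randomised, which is 63% of it (298/474). The 80% power for 3 points remains the only operating characteristic on the page, and a reader of the results will take it as the trial's sensitivity unless told otherwise.

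There is a second trap. The 298 randomised exceed 284 (2 × 142), so the requirement can look met. It is met only if almost nobody is lost, while the plan itself assumes 40% loss.

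At stake is how a null result on a primary outcome is read. At 60% power a true 3-point benefit is missed about 40% of the time, not 20%.

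**Working it through.** **Inputs from the article.** Difference 3, SD 9.0, alpha 0.05, power 80%, loss 40%, 404 sign-ups, 148 and 150 randomised. Sidedness is not stated: a two-sided test reproduces 142, while a one-sided test would give 112. Two-sided is used throughout.

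**1. The plan's own figures.**
- n per group = 2 × (1.96 + 0.8416)² × (9/3)² = 141.3, so 142 (t-test version 142.2).
- 142 / (1 − 0.40) = 236.7, so 237.

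Both are right.

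**2. Analysed numbers for the enrolment achieved.**
- 40% loss after randomisation: 148 × 0.6 = 88.8 and 150 × 0.6 = 90, so about 89 and 90.
- 40% counted from sign-up: 404 × 0.6 = 242.4, so about 121 per group.

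**3. Unadjusted power for 3 points** (two-sample t-test). The standard error is 9 × √(1/n₁ + 1/n₂). The normal approximation to the detectable difference is 2.80 × SE; the table gives the slightly larger t-based value.

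| Analysed per group | SE | Power for 3 points | Difference detectable at 80% |
|---|---|---|---|
| 148 / 150 (no loss) | 1.04 | 82% | 2.93 |
| 121 / 121 | 1.16 | 73% | 3.25 |
| 89 / 90 | 1.35 | 60% | 3.79 |

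Between the extremes, losses of 10%, 20% and 30% from 148/150 give power of about 78%, 73% and 67%.

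**4. Retention needed for 80%.** 284 / 298 = 95.3%, so at most about 4.7% may be lost.

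**5. Effect of baseline adjustment.** With baseline-outcome correlation r, the working SD becomes 9 × √(1 − r²). The article gives no r, so these values are assumptions.

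| r | SD used | Power at 89/90 | Power at 121/121 |
|---|---|---|---|
| 0.3 | 8.59 | 64% | 77% |
| 0.5 | 7.79 | 73% | 85% |
| 0.6 | 7.20 | 79% | 90% |

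80% is reached at about r = 0.61 with 89/90 and at about r = 0.39 with 121 per group.

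**6. What a non-significant result could say.** At 89/90, unadjusted, the 95% interval half-width is about 2.66 points. The upper limit falls below 3 only if the estimate is below 3 − 2.66 = 0.34. A positive estimate between 0.34 and 2.66 would be non-significant and still compatible with a 3-point benefit. At 121 per group the half-width is 2.28, and the cut-off is 3 − 2.28 = 0.72.

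**The case against.** Four points can fairly be made for the article.

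- **It is a planning statement.** The paragraph is in the past tense, describes what was calculated and aimed for, and is numerically correct. A reader might infer that the authors claim 80% power for the achieved sample, or that they miscalculated. The text supports neither. This stands, so the fault is only a missing update.
- **The shortfall is disclosed.** The sign-up number, the baseline number, the group sizes and the admission of under-recruitment are all there. This also stands: nothing is hidden. But the disclosure stops at the head count, and its consequence for power is left to the reader.
- **60% is the least favourable reading.** The article uses its word for recruitment both for the target and for the 404 sign-ups, so some of the 40% may already have happened before baseline (404 to 298 is a 26% fall). The other reading is more natural, because groups exist only after randomisation and loss to follow-up normally means loss from them. The wording is nevertheless ambiguous, and both counts should be shown. Unadjusted power is below 80% on either.
- **The planned analysis is not an unadjusted t-test.** Baseline-adjusted mixed models can recover power, and on the 121-per-group count a moderate correlation would restore 80%. This stands as a possibility. The article gives no correlation, so it cannot be relied on or dismissed.

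Two further inferences go too far. One is that a non-significant result could not exclude a 3-point effect: an estimate close enough to zero would exclude it. The other is that the borrowed SD should simply be replaced by the trial's baseline SD. The 3-point margin was set on the borrowed score, and the article does not show that the trial's own score is on the same scale, or that it is complete for all 298.

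**Conclusion.** The point holds as a calculation left un-updated, not as an arithmetic error. Under the plan's own method, SD and loss rate, unadjusted power for 3 points is about 60% or about 73%, depending on where the 40% is counted from; 80% power then applies to about 3.8 or 3.25 points. With baseline adjustment at assumed correlations of 0.3 to 0.6, power runs from about 64% to 79% on the smaller count and from about 77% to 90% on the larger. It would therefore be wrong to state flatly that the trial has 60% power, and equally wrong to leave 80% as the only figure. These results rest on a two-sided test, SD 9.0 and equal loss in both groups.

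**What to change.** Keep the original calculation and label it as the planning target. Then add a sentence along these lines, choosing one count as the main case:

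> With 298 randomised (148 and 150), 40% loss after randomisation would leave about 89 and 90 per group: unadjusted power for a 3-point difference is about 60%, and 80% power applies to about 3.8 points. If the 40% is counted from the 404 sign-ups, about 121 per group remain, with power about 73% and a detectable difference of about 3.25 points. Baseline adjustment raises these to about 64–79% and 77–90% respectively for assumed baseline-outcome correlations of 0.3 to 0.6.

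Say explicitly which count the 40% applies to. State that a non-significant diet-quality result will be interpreted from the 95% confidence interval relative to 3 points.

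The pooled baseline SD, with the arms combined, may be reported as a sensitivity figure, but only if the trial's score is on the same scale as the score on which the 3-point margin was set.

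The cost is a short calculation and a less favourable stated power. No extra participants are needed, and randomisation, outcomes and models do not change.
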